## Introduction

1

With the change in lifestyles, hypertension, hyperglycemia, hyperlipidemia, smoking, lack of exercise, aging of population, and other risk factors, the incidence of coronary heart disease is increasing year by year, and it has become 1 of the main diseases that affect global health.^[1]^ Myocardial infarction is 1 of the cardiovascular diseases with the highest mortality,^[2]^ and it is a serious threat to people's life and health.^[3]^ Early intervention and standardized drug treatment has greatly reduced the mortality of patients with myocardial infarction, but there is a lack of attention to rehabilitation after the onset of disease. Most patients with myocardial infarction fear exercise, resulting in decreased activity tolerance, decreased cardiopulmonary function, anxiety, decreased quality of life, relapsed illness, and often require hospitalization, which brings a heavy burden to the patient's family and society.^[4]^ Therefore, there is an urgent need to find a method that is simple and easy to operate, with less side effects, that can improve patients’ cardiac function and exercise tolerance, thereby improving the quality of life.

Tai Chi, originated in ancient China, is mainly divided into 5 schools: Chen, Yang, Wu, Wu, and Sun. It is divided into 24 styles, 36 styles, and 108 styles. It is a medium-strength defensive exercise,^[5]^ with the characteristics of health care, economy and convenience.^[6,7]^ Studies have found that Tai Chi exercise can increase patient endurance, balance and sensitivity, and improve the quality of life of patients.^[8,9]^ At the same time, moderate-intensity aerobic exercise is the core content of cardiac rehabilitation, which can not only enhance the relative adaptability of heart function, but also improve the blood supply capacity of the coronary artery of the heart to a certain extent, and reduce the cardiovascular mortality rate by 20% to 30%.^[10]^ As an ancient exercise training, Tai Chi has the characteristics of ease and softness, smoothness and unobstructed intention, which is convenient for patients’ participation and persistence. It has advantages for the rehabilitation of patients with myocardial infarction, but there is currently a lack of large sample comparisons in the academic community.

Therefore, we plan to evaluate the efficacy and safety of Tai Chi on the cardiac function of patients with myocardial infarction through this randomized controlled trial.

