### Sample size

2.4

According to the calculation formula:

$${\text{n}}_{1}=\pi (1-\pi ){\left[\frac{\left(\mu_{1-\alpha }+\mu_{1-\beta }\right)}{\delta }\right]}^{2}\frac{\left(1+\text{c}\right)}{\text{c}},{\text{n}}_{2}=\text{c}{\text{n}}_{1}$$

Using the superiority test, $\mu_{1-\alpha }=1.64,\mu_{1-\beta }=1.28.\pi =0.8,c=1,\delta =0.15$, calculate n1 = n2 = 122. Considering the clinical dropout rate of about 10%, a total of 272 cases need to be included. The included patients will be numbered according to the order of visits, and will be divided into an experimental group and a control group using a completely random method, with 136 cases in each group.

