#### Adverse reaction rate

2.6.2

Including any uncomfortable symptoms (such as dizziness, nausea, etc) during treatment.

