### Study quality control

2.8

Throughout the experiment, each participant will be monitored for safety. All adverse events will be transferred to the clinical trial institution ethics committee of the office, who will review the event and rule on causality. We set up a Data and Safety Monitoring Board (DSMB). Members of DSMB include physicians, clinical pharmacists, test method experts, statistical experts, and members of the ethics committee, who will conduct a risk assessment and safety analysis procedures based on termination conditions.

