### Statistical analysis plan

2.9

The database is established by Excel. The full analysis set refers to the intent-to-treat analysis of all subjects randomly enroll, treat at least once and visit at least once. Per-protocol set: includes all subjects who comply with the trial protocol, have no missing baseline variables, and can measure the main variables. safety set: including random enrollment, at least 1 medication, and at least 1 safety visit after medication.

In this study, SPSS25.0 statistical analysis software will be used for data analysis. If the measurement data meet the normal distribution, the independent sample *t* test is used between the groups, and the paired sample *t* test is used within the group. The results are represented by ($\bar{X}\pm S$); Nonparametric test will be used for those who did not meet the normality, and the results will be expressed in quartiles; Chi square test will be used for counting data. The incidence of adverse events will be compared by chi square test. *P* *<* *.05*, with statistical significance.

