Tai Chi is a traditional boxing skill integrating internal and external cultivation and fighting to strengthen the body. Theoretically, it adheres to the yin-yang syndrome differentiation of ancient Chinese philosophy and the Taoist concept of “Tai Chi”, and also coincides with the Yin-Yang and 5 elements and meridian theory of traditional Chinese medicine. When exercising, hardness and softness are combined with movement and static. It can not only fight the enemy for self-defense, but also cultivate body and mind. It has the functions of relaxing meridians, promoting qi and activating blood circulation. Scholars have found that Tai Chi exercise for 2 years in patients with hypertension and hyperlipidemia can effectively control blood pressure and blood lipid.^[20]^ Practicing Tai Chi in patients with heart disease can help restore aerobic endurance,^[21]^ improve myocardial contraction strength, improve heart blood pumping function, and comprehensively regulate heart and lung by improving respiratory circulation.^[22]^ At the same time, Tai Chi is safe for stable elderly patients with congestive heart failure (NYHA II), and exercises exercise ability and muscle strength at the same time.^[23]^ Compared with other exercise or no exercise, Tai Chi can better improve the quality of life and depression of such patients.^[24,25]^ It is a recommended rehabilitation exercise method.^[26]^

This randomized controlled trial is to verify that Tai Chi can improve the cardiac function of patients with myocardial infarction. Since there is no standard large-sample clinical study to evaluate the effect of Tai Chi on the cardiac function of patients with myocardial infarction, we plan to evaluate its efficacy and safety through prospective randomized controlled studies.

This study also has some limitations: the follow-up time is short, and we cannot understand the impact of long-term efficacy. Therefore, we may extend the follow-up time if necessary.

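### The only between-arm comparison named for adverse events is a chi-square test at P<.05, which cannot say how much excess harm is excluded; a risk difference with a 95% interval should carry the safety reading

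*Protocol article*

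**What the plan says.** The Introduction states the aim: "we plan to evaluate the efficacy and safety of Tai Chi on the cardiac function of patients with myocardial infarction". The Discussion repeats it: "we plan to evaluate its efficacy and safety through prospective randomized controlled studies".

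Section 2.9 (Statistical analysis plan) names one method for the safety comparison: "The incidence of adverse events will be compared by chi square test". It sets P<.05 as the threshold for significance and does not state sidedness. It gives no effect measure, interval, margin or upper bound for adverse events.

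Section 2.6.2 defines the adverse reaction rate broadly: "Including any uncomfortable symptoms (such as dizziness, nausea, etc) during treatment". No expected rate is given.

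Section 2.4 sizes the trial on the total effective rate alone, then allows for losses: "Considering the clinical dropout rate of about 10%, a total of 272 cases need to be included".

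Section 2.8 adds monitoring of each participant, ethics-committee review of all adverse events with a ruling on causality, and a DSMB "who will conduct a risk assessment and safety analysis procedures based on termination conditions".

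**The concern.** The null hypothesis of a chi-square test is equal incidence. Rejecting it is evidence of a difference. Failing to reject it is compatible both with no excess and with a substantial one, and the P value does not tell these apart. A safety aim needs an answer to a different question: how large an excess under Tai Chi do the data fail to exclude? The stated method does not produce that number.

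The sample size was not chosen with adverse events in mind, so whether the test would notice a relevant excess is left to the event rate. If the report ends with no significant difference in adverse events, readers caring for patients after infarction have no way to see how much harm that result leaves open.

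**Working it through.** **1. The plan's own sample size.** Inputs from section 2.4: π = 0.8, δ = 0.15, c = 1, normal quantiles 1.64 and 1.28.

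n = 0.8 × 0.2 × [(1.64 + 1.28)/0.15]² × 2 = 121.3, rounded up to 122 per arm. With 10% dropout, 122/0.9 = 135.6, so 136 per arm and 272 in total. The stated figures reproduce. None of the inputs concerns adverse events.

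**2. Chance that the test misses a true excess.** The control rate is an assumption, because the protocol gives none. Two independent binomial counts are taken with n per arm, and every 2×2 table is enumerated. A table rejects if the Pearson chi-square without continuity correction exceeds 3.841 (two-sided .05). The miss probability is 1 minus the total probability of the rejecting tables.

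Hand check by normal approximation for 10% vs 20%, n = 136. The standard error under the null is √(2 × 0.15 × 0.85/136) = 0.0433. Under the alternative it is √[(0.10 × 0.90 + 0.20 × 0.80)/136] = 0.0429. Then z = (0.10 − 1.96 × 0.0433)/0.0429 = 0.35, so power is about 64% and the miss about 36%. Exact enumeration gives 35.5%.

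A doubling of the control rate:

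| Control vs Tai Chi | Missed, 136 per arm | Missed, 122 per arm |
|---|---|---|
| 2% vs 4% | 86% | 87% |
| 5% vs 10% | 65% | 69% |
| 10% vs 20% | 36% | 40% |
| 15% vs 30% | 15% | 19% |
| 20% vs 40% | 4–5% | 7% |
| 30% vs 60% | under 1% | under 1% |

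At high control rates a doubling is a very large absolute harm, so a fixed 10-point excess is the fairer test there:

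| Control vs Tai Chi | Missed, 136 per arm |
|---|---|
| 15% vs 25% | 45% |
| 20% vs 30% | 52% |
| 30% vs 40% | 59% |

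With a continuity correction the misses are larger: 5% vs 10% at 136 per arm rises from 65% to 74%.

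**3. What an interval adds.** Take 14/136 on Tai Chi against 7/136 on control. The pooled rate is 21/272 = 0.0772, chi-square = 2.53, P = .11: not significant. The risk difference is 7/136 = 5.1 points, with Newcombe 95% interval −1.4 to 11.9 points. The risk ratio is 2.0 (0.83 to 4.80). The test reports no difference; the interval shows that an excess of nearly 12 points is not excluded.

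**4. What the interval would show if the arms were equal.** At 14/136 in each arm (about 10%), the Newcombe interval is ±7.4 points. At 41/136 in each arm (about 30%), it is ±10.8 points. Even perfectly balanced observed rates leave an upper limit of about 7 to 11 points over this range.

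**The case against.** Four points can fairly be made for the plan.

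- **No rule equates non-significance with safety.** A reader might infer that P>.05 will be reported as safe. The document does not say so. It says only that incidence will be compared and that safety will be evaluated, and testing adverse events for a difference is conventional. This stands: the point concerns what the named test can support, not a stated decision rule.
- **The chi-square test is not the whole of the safety evaluation.** Section 2.8 adds individual monitoring, causality review and a DSMB, and section 2.5 adds telephone follow-up for cardiovascular events and rehospitalization. It would be too strong to say that safety is settled by this test alone. But none of these is described as an estimate of the difference between arms at the end of the trial.
- **The event rate could be high.** With any uncomfortable symptom counted over 24 weeks, a control rate of 15% or more is plausible, and a doubling would then usually be detected. So it cannot be claimed in general that the likely result is no significant difference even if Tai Chi doubles events: already at 10% vs 20% the test is more likely to detect it than not. What remains is that a 10-point excess from such rates is still missed about half the time.
- **This is a condensed article.** The full plan may specify intervals, and their absence here is not in itself an error. The objection is therefore to the method the article does state as the comparison, which would remain unsuited to a safety conclusion even if other output were added.

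**Conclusion.** The point holds in limited form. Safety is a stated aim, and the one between-arm comparison named for adverse events cannot bound excess harm. A non-significant result could therefore not support a safety conclusion, whatever the true event rate.

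The size rests on assumed control rates, two-sided testing at .05 without continuity correction, and 136 per arm. For control rates of 2% to 10%, a doubling is missed about 86% to 36% of the time. From 15% upward a doubling is usually detected (missed about 15% or less), but a 10-point excess from 15% to 30% is missed about 45% to 59%. With 122 per arm the misses are generally a few points higher.

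The change is worth making because it is almost free. It corrects what the reported result can be used for; it does not imply that the trial is too small or that its authors intend to misread a P value.

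**What to change.** In section 2.9, replace the adverse-event sentence with wording such as:

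*The proportion of patients with at least one adverse event will be reported by arm, with the risk difference (Tai Chi minus control) and its two-sided 95% confidence interval (Newcombe). Safety will be interpreted from the upper limit of this interval, the largest excess that the data do not exclude. The chi-square P value is descriptive, and a non-significant result will not be taken as evidence of safety.*

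If the full analysis plan already provides such an interval, it is enough to say so here and to state that the safety reading rests on it.

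Cost: a few sentences and one extra interval in the output, with no additional patients or data. The price is a more cautious safety statement. With equal observed rates, the report would have to say that an excess of up to about 7 points (rates near 10%) or about 11 points (rates near 30%) is not excluded.

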## Discussion

3

The rapid development of interventional technology has significantly improved the treatment effect of patients with myocardial infarction and reduced the mortality rate. However, medical treatment and cardiac revascularization cannot completely solve the problems of rehospitalization and quality of life of patients with myocardial infarction. In patients with myocardial infarction, myocardial cells are repeated ischemic and hypoxic for a long time, cardiac output decreases, ventricular remodeling, heart failure, and death can occur in severe cases.^[14,15]^ The results of a study show that drinking, smoking, low vegetable intake, low exercise, and high psychological stress are important risk factors that affect the occurrence of myocardial infarction on a global scale.^[16]^ A healthy lifestyle and diet can prevent and control myocardial infarction.^[17]^ Therefore, prevention and recanalization of blocked blood vessels is the key to the treatment of myocardial infarction, and the earlier the period of cardiac rehabilitation, the greater the benefit.^[18,19]^ Tai Chi is an economical, simple and convenient form of cardiac rehabilitation that can be exercised at home. It has gradually become a popular trend.

Tai Chi is a traditional boxing skill integrating internal and external cultivation and fighting to strengthen the body. Theoretically, it adheres to the yin-yang syndrome differentiation of ancient Chinese philosophy and the Taoist concept of “Tai Chi”, and also coincides with the Yin-Yang and 5 elements and meridian theory of traditional Chinese medicine. When exercising, hardness and softness are combined with movement and static. It can not only fight the enemy for self-defense, but also cultivate body and mind. It has the functions of relaxing meridians, promoting qi and activating blood circulation. Scholars have found that Tai Chi exercise for 2 years in patients with hypertension and hyperlipidemia can effectively control blood pressure and blood lipid.^[20]^ Practicing Tai Chi in patients with heart disease can help restore aerobic endurance,^[21]^ improve myocardial contraction strength, improve heart blood pumping function, and comprehensively regulate heart and lung by improving respiratory circulation.^[22]^ At the same time, Tai Chi is safe for stable elderly patients with congestive heart failure (NYHA II), and exercises exercise ability and muscle strength at the same time.^[23]^ Compared with other exercise or no exercise, Tai Chi can better improve the quality of life and depression of such patients.^[24,25]^ It is a recommended rehabilitation exercise method.^[26]^

This randomized controlled trial is to verify that Tai Chi can improve the cardiac function of patients with myocardial infarction. Since there is no standard large-sample clinical study to evaluate the effect of Tai Chi on the cardiac function of patients with myocardial infarction, we plan to evaluate its efficacy and safety through prospective randomized controlled studies.

This study also has some limitations: the follow-up time is short, and we cannot understand the impact of long-term efficacy. Therefore, we may extend the follow-up time if necessary.

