### Interventions

2.5

This study will select patients who meet the criteria of this study by recruiting in the hospital. A randomized controlled study will be used, in which the control group: conventional treatment; the experimental group: Tai Chi exercise will be added to the control group. The 2 groups of patients will receive the same routine care. During the trial period, avoid smoking, alcohol and irritating food, avoid strenuous exercise, and pay attention to adverse reactions. When necessary, the attending doctor can appropriately adjust the plan according to the patient's condition, and all intervention methods will be recorded in detail for the final result analysis. Efficacy assessors are not aware of the study group plan, and data statisticians are not involved in the design and implementation of the study. Before and after treatment, the health status of each patient will be evaluated, including the outcome indicators, and all patients will be followed up by telephone. Follow-up content includes cardiovascular events and rehospitalization.

Control group: according to the relevant guidelines after myocardial infarction intervention, standard drug treatments will be given, including antiplatelet drugs, statins, angiotensin converting enzyme inhibitors, nitrates, β-receptor blockers, and health education. The content of the education includes the control of myocardial infarction risk factors, techniques for improving sleep quality, diet guidance, etc, and pays attention to communicating with patients, mastering their psychological and emotional changes, and avoiding or alleviating bad moods such as anxiety and depression in elderly patients.

Experimental group: on the basis of conventional treatment, the experimental group will be given 24 simplified Tai Chi. Professional Tai Chi teachers will teach and practice the subjects to ensure that the practice time and movement rhythm are basically the same. The whole set of Tai Chi includes 3 parts: preparation activity, training activity and end activity, totaling about 20 minutes, twice a day, once in the morning and once in the afternoon, and lasts for 24 weeks.

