#### Efficacy indicators

2.6.1

Main efficacy indicators: total effective rate: referring to the “Guiding Principles for Clinical Research of New Chinese Medicines”,^[13]^ total effective rate = (marked effective number + effective number)/total number × 100%. According to NYHA grading method, evaluate the curative effect of cardiac function: ① Marked effective: cardiac function improved by more than grade 2; ② Effective: cardiac function improved by grade 1, but not as good as grade 2; ③ Ineffective: cardiac function improved less than grade 1; ④ Deterioration: the deterioration of heart function is less than grade 1.

Secondary efficacy indicators: 6 minutes walking test, brain natriuretic peptide, left ventricular ejection fraction, medical outcomes study short-form36 (SF-36).

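### The planned claim of improved cardiac function rests on NYHA class, which depends largely on what unblinded patients report; word the primary conclusion as NYHA functional class and tie any wider claim to tested LVEF and BNP

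*Protocol article*

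**What the plan says.** **Aim.** The Discussion (section 3) of the protocol article says: "This randomized controlled trial is to verify that Tai Chi can improve the cardiac function of patients with myocardial infarction".

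**Primary endpoint.** Section 2.6.1 (Efficacy indicators) names one main indicator, the total effective rate: "total effective rate = (marked effective number + effective number)/total number × 100" percent. The scale behind it is given as "According to NYHA grading method, evaluate the curative effect of cardiac function". The lower of the two responder categories is "cardiac function improved by grade 1, but not as good as grade 2", so a gain of one class is enough.

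**Other measures.** The same section lists "Secondary efficacy indicators: 6 minutes walking test, brain natriuretic peptide, left ventricular ejection fraction" and SF-36. Section 2.7 has data collected before treatment, at 12 weeks and at 24 weeks.

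**Comparison.** Section 2.5 (Interventions) describes an add-on design: "the control group: conventional treatment; the experimental group: Tai Chi exercise will be added to the control group". For the experimental arm, "Professional Tai Chi teachers will teach and practice the subjects to ensure that the practice time and movement rhythm are basically the same", and a set of about 20 minutes is scheduled twice a day for 24 weeks. The control arm receives drugs and health education, including communication with patients about mood.

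**Blinding.** Section 2.5 says: "Efficacy assessors are not aware of the study group plan". No blinding of patients is stated. Consent precedes randomization (section 2.2), and people who cannot understand the research plan are excluded (section 2.3).

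**Limitations.** The Discussion names only the short follow-up.

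**The concern.** The claim and the endpoint do not measure quite the same thing. The Discussion explains the expected benefit in terms of myocardial contraction and pumping, so a reader will take improved cardiac function as a statement about the heart. NYHA class grades symptoms and limitation in daily activity. An assessor who does not know the arm still grades largely from the account of a patient who does.

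The protocol itself supplies another route to a better NYHA class. The Introduction says that most patients after infarction fear exercise and links this to anxiety and lower activity tolerance. The Discussion cites benefits of Tai Chi for depression in patients with heart disease. Less fear or better mood could raise reported capacity without any change in the heart. That may be a real benefit to patients, but it would not show improved cardiac function in the sense the Discussion gives it.

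At stake is what a positive primary result may be said to show.

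**Working it through.** **1. The plan's own figure.** Inputs from section 2.4: z-values 1.64 and 1.28, π = 0.8, δ = 0.15, c = 1.

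n per arm = 0.8 × 0.2 × (2.92 / 0.15)² × 2 = 121.26, rounded up to 122. With 10% dropout: 122 / 0.9 = 135.6, rounded up to 136 per arm, 272 in total. The stated sample size reproduces and is not at issue.

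**2. Links in the argument.**

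| Link | Source |
|---|---|
| Claim concerns cardiac function | Section 3 |
| Sole primary endpoint is a gain of at least one NYHA class | Section 2.6.1 |
| NYHA class rests largely on patient report | General knowledge of the scale; not stated in the protocol |
| Patients know their arm | Follows from the intervention in section 2.5 |
| Only assessors are stated to be blinded | Section 2.5 |
| No activity in the control arm matched to Tai Chi | Section 2.5 |
| LVEF and BNP are secondary | Section 2.6.1 |

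**3. Sensitivity to a reporting shift (illustration).** Assume no true effect, a responder rate of 0.8 and 122 per arm. Let b be the excess proportion of Tai Chi patients reported as one class better. The protocol gives no value for b; the values below are assumptions.

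SE = √(2 × 0.8 × 0.2 / 122) = 0.0512.

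Two-sided false positive rate = P(|Z + b/SE| > 1.96). One-sided rate = P(Z + b/SE > 1.64).

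| b | b/SE | Two-sided P<.05 | One-sided 1.64 |
|---|---|---|---|
| 3 points | 0.59 | 9% | 15% |
| 5 points | 0.98 | 16% | 25% |
| 7.5 points | 1.46 | 31% | 43% |

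Both columns are shown because section 2.4 uses 1.64 while section 2.9 states P<.05 with a chi-square test.

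**4. Other control rates.** With assumed control rates of 0.65, 0.725 and 0.80, and the variance taken at the shifted rate, a 5-point shift gives 13–18% two-sided and 21–27% one-sided. The smallest observed excess that reaches significance is 11–14 responders of 122 two-sided, or 10–12 one-sided.

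**5. Amount of practice.** If practice takes place every day, 24 weeks × 7 days × 2 = 336 scheduled occasions. This counts practices, not contacts with a teacher.

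**6. Why a supportive endpoint must be tested.** Suppose the wider claim were allowed whenever LVEF or BNP merely pointed towards Tai Chi. With no effect on either, at least one would do so in 50% of trials if the two were perfectly correlated, and in 1 − 0.5 × 0.5 = 75% if independent. Direction alone would let through much of what it should stop.

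**The case against.** The strongest defence is that the protocol uses cardiac function as its own term for NYHA grade, in section 2.3 as well as 2.6.1, and takes its response categories from a cited guideline. An add-on comparison with usual care is a legitimate design, and patients cannot be blinded to exercise. This stands as a defence of the design and of NYHA class as an endpoint. It does not answer the wording: the Discussion ties the term to contraction and pumping, and readers will do the same.

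Several stronger readings are tempting, and the document does not support them.

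- *Blinding is worthless here.* It is not: blinded assessors remove their own bias. Only the patient-reporting route stays open.
- *LVEF and BNP will be ignored, and a NYHA difference without them would be reported as proof.* No section states such a rule. Both are named secondary indicators measured at the same times as the primary, so a discordant result would be visible. What can be said is that the primary conclusion does not depend on them.
- *The Tai Chi arm has some 336 taught sessions and the control arm no attention.* Section 2.5 does not say how many practices are teacher-led, and the Discussion notes that Tai Chi can be done at home. The control arm receives education and communication about mood, and both arms have the same routine care and telephone follow-up. The size of the contact difference cannot be determined.
- *A positive result would probably be expectation or attention alone.* Nothing in the document gives the size of such an effect. Any binary endpoint with this standard error would yield the same illustrative figures. Grade I patients are eligible and cannot improve, so a shift would have to come entirely from grades II and III.

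How NYHA is elicited, and whether assessors record a guess of the arm, are operational details that an article may leave to the full protocol. They are not part of this point.

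**Conclusion.** The point holds as a mismatch between the claim and the endpoint. A positive primary result would support improved NYHA functional class with Tai Chi added to usual care. Because patients know their arm and contact is not matched, it would not by itself show improved cardiac function in the physiological sense.

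The size of any bias is unknown. Under an assumed 5-point shift, with no true effect, π = 0.8 and 122 per arm, the false positive rate is about 16% two-sided (25% one-sided). This shows sensitivity, not likelihood. The conclusion also rests on the general property of NYHA class that it depends largely on patient report.

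This does not invalidate the design. It is a change worth making because it costs little and settles beforehand what the trial can conclude.

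**What to change.** - **Abstract and section 3:** word the primary conclusion as improved NYHA functional class for Tai Chi added to usual care. Name unblinded patients and unmatched contact as a limitation beside short follow-up.
- **Section 2.6.1:** name week-24 LVEF, then week-24 BNP, as key supportive endpoints. Test them between arms in that fixed order at P<.05, and only after a positive primary result. BNP is then tested formally only if LVEF is significant.
- **Section 2.6.1:** reserve any claim of improved cardiac function beyond NYHA class for a statistically significant difference in this sequence. A favourable direction is not enough.

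**Cost:** wording, and an order for two endpoints already collected; no extra patients, visits or tests. The downside is a narrower claim if LVEF and BNP do not differ. The trial was not sized for either, so a non-significant result there would not show absence of an effect.
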